#### Liver histology

An independent blinded liver pathologist is determining the NAFLD Activity Score^37^ and liver fibrosis stage. This is then compared to the clinical biopsy report. Interobserver agreement is determined by a formal Kappa calculation (>0.7 will be considered agreement). The AMPK pathway will be analyzed from the liver biopsy specimen. From liver tissue, the abundance of specific mRNAs will be assessed by Predesigned TaqMan Real-time PCR assays using our current methods.^38^ Specimens will be placed in RNA*later* Stabilization Solution. RNA will be isolated using a PureLink RNA Mini Kit. RNA quality will be assessed (Agilent 2100 Bioanalyzer) as will the abundance of specific mRNAs (eg, Acetyl-CoA carboxylase 1, sterol regulatory element-binding protein-1, carbohydrate-responsive element-binding protein, peroxisome proliferator-activated receptor-γ coactivator 1α, acyl-CoA dehydrogenase medium chain). RNA will be stored as ethanol precipitates (−20 °C) and protein (−80 °C) after boiling in SDS sample buffer until analysis. AMPK activation and AMPK (both phosphorylated and unphosphorylated) as well as Acetyl-CoA carboxylase 1 protein expression will be assessed by western blot.^39^ Approximately 50 mg of tissue will be homogenized in buffer containing a mixture of protease and RNase inhibitors. After centrifugation, equal amounts of protein will be resolved on SDS polyacrylamide gels and transferred to PVDF membrane. The membrane will be stained to confirm equal protein loading, destained, and then blocked (5% nonfat dry milk). The membrane will be probed with validated primary antibodies (followed by secondary antibody and visualized using Clarity Western ELC Blotting Substrate. Protein abundance will be expressed relative to either total protein or, for phospho-proteins, to the total amount of the specific protein. AMPK activation will be assessed by western blot using anti-phospho-AMPK substrate motif antibody.

We will assess colocalization of glycogen and AMPK by immunofluorescence microscopy using a fusion protein (GYSC) containing glutathione S-transferase, a cMyc epitope and the carbohydrate-binding module from starch-binding domain-containing protein 1, for use as a glycogen-binding probe.^40^ The GYSC probe has a glutathione s-transferase-tag that will be visualized using a fluorescent anti-glutathione s-transferase antibody. A fluorescently tagged anti-rabbit antibody will be used to visualize AMPK. The results of this analysis are expected to provide direct support for the hypothesis that exercise-induced depletion of liver glycogen leads to dissociation of AMPK from glycogen and its subsequent activation. While we expect to be able to localize glycogen signal to the hepatocytes based on cell morphology, we will also stain with a fluorescently labeled antibody against hepatocyte-specific antigen as confirmation. Because AMPK activation can inactivate fibrogenic HSCs, we will perform additional exploratory analysis using mRNA extraction and real-time PCR to measure αsmooth muscle actin, peroxisome proliferator-activated receptorγ, and collagen-1α, which are validated markers of HSC activity.^41^

#### MR-glycoCEST

In order to standardize glycogen measurement via glycoCEST,^42^ we are using the following validated methods as a part of the study protocol.^43^ On the day prior to metabolic and glycogen testing, all subjects are instructed to consume 55% of their calories from carbohydrates. On the evening prior, subjects are provided a standard final meal consumed the evening before testing to standardize macronutrient intake across participants (Nestle Boost Very High Calorie, 237 mL, Nestle Inc, Bridgewater, NJ). Subjects submit a photo to research staff to document their completion of the shake. Subjects then perform their exercise session the next morning followed immediately by completion of glycoCEST measured glycogen of both the liver and the calf muscle. Given the interplay between the liver and the skeletal muscle, it is important to examine this relationship in greater detail as depletion of muscle glycogen may lead to further mobilization of liver glycogen as a source of glucose that can be delivered via the bloodstream for exercise performance. For this reason, we have decided to measure calf skeletal muscle glycogen with glycoCEST (at the same timepoints that liver glycoCEST glycogen measurement is occurring) as this is a validated, reliable noninvasive method.^42^ The time between final meal and exercise session is standardized and is no longer than 12 hours, given this is the amount of time it takes for fasting to deplete liver glycogen.^44^

GlycoCEST measurements is being performed using the same Siemens 3T PrismaFit system (Siemens Healthineers, Erlangen, Germany) that will be used to measure MRI-PDFF. A single-slice chemical exchange saturation transfer (CEST) sequence is employed to quantify the glycoCEST effect. Sequence parameters in the liver include a repetition time of 4200 ms, spatial resolution of 2.5×2.5×8 mm, CEST preparation duration of 500 ms, CEST preparation amplitude of 1.25 uT,^45^ and the z-spectrum are sampled from −4 to 4 PPM with 32 samples, including a S0 image. In the calf muscle sequence parameters include a repetition time of 7000 ms, spatial resolution of 1.25×1.25×8 mm, CEST preparation duration of 500 ms, CEST preparation amplitude of 1 uT,^42^ and the z-spectrum are sampled from −4 to 4 PPM with 41 samples, including a S0 image.

The CEST z-spectrum data are analyzed offline with custom software developed in Matlab, from which the mean MTR asymmetry value will be calculated in select region of interests in the liver tissue and calf skeletal muscle. A previously described technique^45^ is being utilized for the correction of the liver z-spectrum data. The simultaneous mapping of the water shift and B1 technique^46^ is being used to correct the calf muscle z-spectrum data.

#### Physical activity and functional capacity assessment

To assess all physical activity and not just that completed as part of the exercise training program, the International Physical Activity Questionnaire^47^ is being administered. International Physical Activity Questionnaire questions pertain to different physical activity domains including home, job-related, sitting, sport, and transportation. Additionally, fitness activity trackers are being provided to each subject to allow for remote monitoring 24 hours a day, 7 days a week. The fitness tracker (FitBit Charge HR, FitBit, San Francisco, CA) has a heart rate monitor and can track step counts, flights of stairs climbed, total distance walked, total duration of activity based on custom heart rate zones established after cardiorespiratory fitness testing, calories expended from physical activity, and resting heart rate. Fitness trackers are also being used to monitor remote exercise sessions if a subject elects to perform this type of session, but only after the approval of the study staff. Physical activity information is being downloaded and reviewed monthly by study staff members. To address functional capacity, the Duke Activity Status Index^48^ questionnaire is also being administered to augment physical activity capture and better understand how physical activity and fitness translate to everyday life for each subject.

#### Quality of life

Because individuals with MASLD exhibit diminished quality of life across all health domains,^49^ subjects in the AMPED study are undergoing assessment using the Patient-Reported Outcomes Measurement Information System Computerized Adaptive Testing tool via tablet computer (iPad). Participants are prompted to reflect on their experiences over the past week in nine distinct health domains, including anxiety/fear, cognitive function, depression/sadness, fatigue, instrumental support, pain interference, physical function, sleep disturbance, and social roles. A standardized protocol is implemented to elucidate the assessment process to participants and offer direct assistance with any technical challenges pertaining to the tablet computer. Our previous work has demonstrated the validity and security of utilizing tablet computers by individuals with MASH performing an exercise intervention.^11^ Real-time scores for each health domain are automatically computed and normalized to the underlying population distribution derived from responses obtained during the 2000 US Census utilizing T-score algorithms provided by the Patient-Reported Outcomes Measurement Information System Assessment Center software.^50^ The median T-score is established at 50, with an SD equivalent to 10.

#### Vital signs

Blood pressure (mm Hg) and heart rate (bpm) are being measured once the subject sits at rest for at least 5 minutes. Blood pressure is obtained using an automated, portable blood pressure and heart rate monitor (Omron HEM 907XL)^51^ or a manual sphygmomanometer (Welch Allyn, Skaneatles Falls, NY). Resting heart rate is obtained by a fitness activity tracker with a heart rate monitor (FitBit, San Francisco, CA). Temperature is measured using a Genius Tympanic Ear Thermometer with Base LCD Display (Cardinal Health, Dublin, OH).

### Covariates

AMPED study participants directly report, or study staff verify self-reported information in the electronic health record documenting their demographics (eg, age, gender, race/ethnicity, education). Past medical, surgical, and social history are reviewed, including smoking status and history of illicit drug use. Medications are also reviewed both from self-report and the electronic health record, including those that are prescribed to treat MASH. Table 3 summarizes captured outcomes and covariates.

**TABLE 3 T3:** Study objectives and end points

End point	Methods
Primary efficacy	
Liver fat	• MRI-PDFF will assess change in liver fat after week 16
Secondary efficacy—key	
Liver and muscle glycogen	• MR-S will assess change in liver and muscle glycogen after week 16
Liver fat and liver stiffness using imaging analysis	• VCTE will assess change in liver fat and stiffness after week 16
Clinically meaningful improvement in liver fat and stiffness	• Proportion of participants with ≥26% relative reduction in VCTE-measured liver stiffness (kPA) after week 16 • Proportion of participants with ≥30% relative reduction in MRI-PDFF after week 16
Circulating biomarkers of hepatic injury	• Change in ALT, AST, CK-18, CRP, IL-6 after week 16 • Proportion of participants with ≥17 IU/L decrease in ALT after week 16
Circulating biomarkers of liver fibrosis and fibrogenesis	• Change in ELF score, Fibrosis-4 index (FIB-4), NFS, PRO-C3, TIMP-1 after week 16
Secondary efficacy—other	
Lipid parameters	• Change in LDL, HDL, triglycerides after week 16
Biomarkers for MASLD comorbidities	• Change in Hemoglobin A1c, insulin, plasma glucose, HOMA-IR, McAuley Index, ASCVD, Framingham score after week 16
Body composition	• Change in total body fat, visceral adipose tissue, subcutaneous adipose tissue, and fat-free mass as measured by DXA after week 16 • Change in waist and hip circumference, skinfolds at weeks 4, 8, 12, 16
Dietary intake and physical activity	• Change in fitness tracker measured step counts, self-reported physical activity (IPAQ, DASI), self-reported dietary intake at weeks. 4, 8, 12, 16
Patient-reported outcomes	• Change in PROMIS after week 16
Adherence	• % of completed exercise sessions after week 16 • % who achieved a priori definition of adherence (>80% session completion) after week 16
Safety	
Safety and tolerability	• Safety and tolerability will be evaluated in terms of adverse events (AE), physical exam, and changes in body weight and/or vital signs at weeks 4, 8, 12, 16

Abbreviations: AE, adverse event; ALT, alanine aminotransferase; Apo, apolipoprotein; ASCVD, atherosclerotic cardiovascular disease; AST, aspartate aminotransferase; CK, cytokeratin; CRP, C-reactive protein; DASI, duke activity score index; DXA, dual x-ray absorptiometry; ELF, enhanced liver fibrosis; FIB-4, Fibrosis-4 index; HOMA-IR, homeostatic model assessment for insulin resistance; IPAQ, international physical activity questionnaire; MASLD, metabolic dysfunction–associated steatotic liver disease; MASH, metabolic dysfunction–associated steatohepatitis; MR-S, magnetic resonance spectroscopy; NFS, NAFLD Fibrosis Score; PDFF, proton density fat fraction; PRO-C3, N-terminal type III collagen propeptide; PROMIS, Patient-Reported Outcomes Measurement Information System; VCTE, vibration-controlled transient elastography.

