### Measures

Table 2 lists the study measures and their timing. All self-reported measures are completed by participants via tablet computer, smartphone, or paper questionnaire should a digital option not be available for whatever reason.

**TABLE 2 T2:** Schedule of activities

Study phase	Screening (4 wk)	Study intervention period (16 wk)					
Visit	**1**	**2**	**3**	**4**	**5**	**6**	**ED**
Study week	−4 to 0	0	4	8	12	16	—
Visit window (d)	—	+/−1	+/−1	+/−1	+/−1	+/−1	—
Type of visit							
Study procedure							
Informed consent	X	—	—	—	—	—	—
Eligibility criteria	X	X	—	—	—	—	—
Demographics	X	—	—	—	—	—	—
Height	X	—	—	—	—	—	—
Weight and BMI	X	X	X	X	X	X	X
Waist and hip circumference	X	—	X	X	X	X	X
Skinfold measurements^a^	X	—	X	X	X	X	X
Medical history	X	X	X	X	X	X	X
AUDIT-C questionnaire	X	—	X	X	X	X	X
Urine pregnancy test	X	—	—	—	—	—	—
Lifestyle counseling	X	X	X	X	X	X	X
Randomization	—	X	—	—	—	—	—
Fitness tracker set-up	—	X	—	—	—	—	—
Liver biopsy	—	—	—	—	—	X	X
Case report forms	X	X	X	X	X	X	X
Safety							
AEs	X	X	X	X	X	X	X
Physical exam	X	X	X	X	X	X	X
Concomitant medications	X	X	X	X	X	X	X
Vital signs	X	X	X	X	X	X	X
ECG	X	—	—	—	—	X	X
Efficacy							
VCTE	X	—	X	X	X	X	X
MRI-PDFF, MRS	X	X	—	—	—	X	X
Circulating biomarkers^b^	X	—	—	—	—	X	X
AMPK pathway^c^	X	—	—	—	—	X	X
Lipid parameters^d^	X	—	—	—	—	X	X
Body composition^e^	X	—	—	—	—	X	X
Cardiorespiratory fitness	X	—	—	—	—	X	X
Behavioral change							
Dietary intake and counseling^f^	X	—	X	X	X	X	X
Physical activity^g^	X	—	X	X	X	X	X
Adherence	—	—	X	X	X	X	X
MASH counseling	X	—	—	—	—	—	—
Patient-reported outcomes							
PROMIS	X	—	X	X	X	X	X

= in-person visit with study staff.

a Skinfolds are obtained at seven sites: chest, abdominal, thigh, subscapular, suprailiac, and midaxillary.

b Liver enzymes (ALT, AST), Adiponectin, CK-18, CRP, ELF, FGF21, FIB-4, IL-6, MASLD comorbidities (A1c, insulin, glucose, HOMA-IR, McAuley Index), PRO-C3,TIMP-1 as well as whole-blood biobanking, NFS, ASCVD score, and Framingham risk.

c AMPK, SREBP1c, ACC, ACADAM, PGC1α, CK-19.

d LDL, HDL, triglycerides.

e Total body fat, visceral adipose tissue, subcutaneous adipose tissue, and fat-free mass as measured by DXA.

f Dietary intake via self-report.

g Fitness tracker measured step counts, self-reported physical activity (IPAQ, DASI).

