### Data analysis plan

We will invoke the intent-to-treat principle for the primary analyses. We will apply an ANCOVA to compare the 3 groups with respect to the MRI-PDFF (primary outcome) and all other continuous secondary outcomes while including the baseline measurement and diabetes status as covariates. We impose a Bonferroni-corrected significance level of 0.017 for the multiple pairwise comparisons of the three groups. We will apply a Mantel-Haenszel test to compare the 3 groups with respect to dichotomous outcomes while accounting for the baseline measurement and diabetes status. A *p*-value of <0.05 will be regarded as statistically significant. As a series of secondary analyses and sensitivity analyses, we will use multiple imputations for estimating missing values in the outcomes variables to assess the robustness of the primary analyses. We will conduct all statistical analyses via SAS version 9.4 (Cary, NC).

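### For VCTE and PROMIS the named week-16 ANCOVA makes no use of the week 4, 8 and 12 values; a repeated-measures model would be a cheap, modest improvement to these secondary analyses

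*Protocol article*

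**What the plan says.** Under Measures, the article states that "Table 2 lists the study measures and their timing". That schedule marks VCTE, PROMIS, waist and hip circumference and skinfolds at screening, weeks 4, 8, 12 and 16, and in the ED column. MRI-PDFF has no visit between week 0 and week 16.

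Table 3 (under Covariates) treats these outcomes in two ways:
- **Week 16 only.** For VCTE, listed as a key secondary: "VCTE will assess change in liver fat and stiffness after week 16". For patient-reported outcomes: "Change in PROMIS after week 16".
- **Every visit.** For anthropometry: "Change in waist and hip circumference, skinfolds at weeks 4, 8, 12, 16". Step counts, self-reported activity and diet follow the same pattern.

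The Data analysis plan then names one model: "We will apply an ANCOVA to compare the 3 groups with respect to the MRI-PDFF (primary outcome) and all other continuous secondary outcomes", with the baseline measurement and diabetes status as covariates. No visit term or repeated-measures model appears. The same section says "We will invoke the intent-to-treat principle for the primary analyses" and places multiple imputation of missing outcomes among the secondary and sensitivity analyses. The article does not say how an ED measurement enters the analysis.

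**The concern.** The model does not match the schedule. For VCTE and PROMIS, three post-baseline measurements per person are collected at some burden to participants and then play no part in the main comparison. A participant last seen at week 12 contributes to that comparison only if an ED value stands in for week 16. Such substitution would mix different lengths of exposure, and leaving it out loses the participant. For waist, hip and skinfolds the endpoint is four correlated values per person, yet the named ANCOVA has no term that would bring them into one analysis. The natural reading is four separate fits per measure.

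What is at stake is some precision, and some protection against dropout related to early response. The plan allows for 20% attrition, which is 9 of 45 participants or 3 per arm. Under Possible limitations it concedes that feasibility of the higher dose is unknown, so dropout related to arm or response is possible.

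**Working it through.** **1. The plan's own figure.** The stated power (at least 90% per pair) concerns MRI-PDFF. Inputs from Sample size and power calculations: differences of 25, 35 and 10 points, SD 6, two-sided level 0.017, 15 per arm, 20% dropout (12 per arm). For the smallest difference the noncentral-t power is 97.4% at 15 per arm and 92.3% at 12; for the other two it is essentially 100%. The figure reproduces. It is not affected by this point, because MRI-PDFF has no interim visits.

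**2. Precision at week 16.** The documents give no within-person correlation. I assume r = 0.5 to 0.9, compound symmetric (CS) or first-order autoregressive (AR) across screening and weeks 4, 8, 12 and 16, with unit SD.

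Let v0 be the week-16 variance given baseline, and R²k the share of v0 explained by the first k interim visits. Let p1 to p4 be the proportions still observed at weeks 4, 8, 12 and 16, with p4 = 0.80. Under monotone dropout, missing at random, the large-sample variance of the repeated-measures contrast relative to the week-16 completer ANCOVA is

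ratio = p4 × [R²1/p1 + (R²2 − R²1)/p2 + (R²3 − R²2)/p3 + (1 − R²3)/p4].

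Example, AR with r = 0.9:
- v0 = 1 − 0.9⁸ = 0.5695.
- Adding weeks 4, 8 and 12 in turn leaves 0.4686, 0.3439 and 0.19, so R² = 0.177, 0.396 and 0.666.
- With dropout of 5% per interval (p = 0.95, 0.90, 0.85, 0.80): 0.80 × (0.187 + 0.243 + 0.318 + 0.417) = 0.932.
- With all dropout after week 12 the formula reduces to 1 − 0.2 × R²3 = 1 − 0.2 × 0.666 = 0.867.

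| Dropout pattern (20% in total) | Variance ratio, range over r and structure | Effective n per arm (12 / ratio) |
|---|---|---|
| 5% in each of four intervals | 0.93–0.98 | 12.2–12.9 |
| All between weeks 12 and 16 | 0.87–0.96 | 12.5–13.9 |
| All before week 4 | 1.00 | 12.0 |
| None | 1.00 | 15.0 |

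If the 20% instead leaves in equal parts after weeks 4, 8 and 12 (p = 1, 0.933, 0.867, 0.80), the AR 0.9 case gives 0.80 × (0.177 + 0.235 + 0.312 + 0.417) = 0.912, about 9% lower variance. Simulation with 15 per arm agrees: the completer ANCOVA had 1.5–9% more variance under random dropout.

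**3. Bias if leaving depends on early response.** In simulation with 15 per arm, 20% dropout and the same correlations, where exercise-arm leavers were poor early responders, the completer ANCOVA favoured exercise by 0.02–0.07 SD. The likelihood repeated-measures estimate had almost no bias.

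A rough ceiling comes from supposing that exactly the worst 20% at week 4 leave. Completers then sit 0.280/0.8 = 0.350 residual SD too high in response at week 4. The week-16 shift is 0.350 × c/√v, where c is the covariance of weeks 4 and 16 given baseline and v the week-4 variance given baseline. For CS 0.7: 0.350 × 0.21/0.714 = 0.10 SD. For AR 0.5: 0.350 × 0.094/0.866 = 0.04 SD. The simulated figures have the right order.

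**4. Scale.** The standard error of a 12-versus-12 contrast is √(2 × v0/12). It runs from √(2 × 0.19/12) = 0.18 (CS 0.9) to √(2 × 0.996/12) = 0.41 (AR 0.5). The bias is well below one standard error.

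**The case against.** A baseline-adjusted ANCOVA at a prespecified endpoint visit is a valid analysis. This is a condensed article, and covariance structures or rules for ED values commonly sit in a SAP that is not shown. The gain is small, rests on assumed correlations and an assumed dropout mechanism, and may not arise: the sample size section expects dropout well under 20%, and Possible limitations cites about 10% in earlier studies. An unstructured model is also demanding with 45 participants. All of this stands and limits the weight of the point. It does not remove it, because the Data analysis plan does fix a model for "all other continuous secondary outcomes while including the baseline measurement and diabetes status as covariates", and that model does not use the interim VCTE and PROMIS values.

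Two stronger readings are tempting, and the documents support neither:
- A reader might infer that interim waist, hip and skinfold data are thrown away. Table 3 makes each visit an endpoint. What is unsettled is only how the four correlated values are analysed together.
- A reader might infer that early leavers are excluded. The article states intent-to-treat, schedules an ED visit that repeats exactly these measurements, and plans multiple imputation. It never describes a completers-only analysis. The supportable statement is narrower: imputation is not the main analysis, and whether ED values fill the gap is not stated.

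**Conclusion.** The point holds as a minor one. For VCTE and PROMIS the named main analysis leaves three scheduled measurements per person unused. For the anthropometric measures it gives no single analysis of the four visits. The likely benefit of changing is about 2–9% lower variance at 20% dropout, up to about 13% in the most favourable late-dropout case examined. It would also avoid roughly 0.02–0.07 SD of bias in favour of exercise, if poor early responders leave the exercise arms. Both figures depend on assumed correlations of 0.5–0.9. The bias figure also assumes that leaving depends on response already observed. There is no gain if everyone completes or all dropout precedes week 4. This is an inexpensive improvement to secondary analyses, not an error, and it does not touch the primary outcome.

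**What to change.** For continuous outcomes scheduled at weeks 4–16, replace the ANCOVA by a mixed model for repeated measures:
- fixed terms for arm, visit, arm by visit, baseline, baseline by visit and diabetes status;
- unstructured covariance, with a prespecified simpler structure if it does not converge;
- Kenward–Roger degrees of freedom;
- the arm contrasts at week 16 as the reported result.

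State how ED measurements are assigned to visits. Keep ANCOVA for outcomes measured only at baseline and week 16, including MRI-PDFF.

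The cost is a few sentences of analysis-plan wording. No new data are needed, and SAS 9.4, already named, fits the model. The downside is a more complex model for 45 participants, which is why the fallback structure should be fixed in advance.

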### Randomization

Subjects for the AMPED study are randomized 1:1:1 to arm 1 (750 MET-min/wk), arm 2 (1000 MET-min/wk), or arm 3 (SOC) for 16 weeks. To account for potential confounding from diabetes,^26^ stratified randomization has been invoked to ensure equal subjects in each group within the nondiabetes and diabetes stratum. Randomization is automatically performed by the study database (REDCap, Vanderbilt University), a secure, web-based application that supports data capture for research studies and serves as a data repository.^27^

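### The change in tracker step counts has no pre-randomization baseline as scheduled, because Table 2 asks for counts at screening but sets the tracker up only at the randomization visit

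*Protocol article*

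**What the plan says.** All of the relevant text is in the protocol article.

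- **End point.** Table 3 (under Covariates), in the group of other secondary efficacy end points below the key ones, lists "Change in fitness tracker measured step counts, self-reported physical activity (IPAQ, DASI"), along with dietary intake, at weeks 4, 8, 12 and 16.
- **Model.** The Data analysis plan applies an ANCOVA to the primary outcome and to "all other continuous secondary outcomes while including the baseline measurement and diabetes status as covariates". Step counts are continuous, so this rule covers them.
- **When steps are assessed.** In Table 2 (under Measures) the row "Physical activity^g" is marked at screening, at weeks 4, 8, 12 and 16, and at early discontinuation. It is not marked at week 0. Footnote g gives the content of the row as "Fitness tracker measured step counts, self-reported physical activity (IPAQ, DASI").
- **When the tracker is issued.** The Table 2 row "Fitness tracker set-up" is marked at visit 2 (week 0) only. Randomization is marked at that same visit.
- **Related timing.** Dietary assessment has patients log food in the tracker's smartphone application after they are randomized, which agrees with set-up at visit 2.

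**The concern.** A change score and a baseline-adjusted ANCOVA both need a value from before treatment assignment. The schedule asks for that value at screening, from a device that the patient does not receive until the randomization visit. The article mentions no run-in wear period and does not say what else would serve as the step-count baseline.

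Two things are at stake. With 15 patients per arm, a baseline covariate can be worth a good deal of precision. And the standard-care patients enter as sedentary by self-report, are counselled towards at least 150 minutes of activity a week, and wear the same tracker. Without a count from before the trial, no tracker reading shows whether their activity rose above its usual level. Only self-report gives a starting point.

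An undefined baseline also invites the analyst to fill the gap later with the first days of wear, which come after randomization.

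**Working it through.** No figure in the plan has to be reproduced. The check compares rows of the schedule and then sizes the loss.

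**1. Rows of Table 2 side by side**

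| Row | Screening | Week 0 (visit 2) | Weeks 4, 8, 12, 16 |
|---|---|---|---|
| Physical activity (footnote g includes tracker steps) | marked | – | marked |
| Tracker set-up | – | marked | – |
| Randomization | – | marked | – |

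Scheduled tracker wear before visit 2 is zero days. If the screening mark is read as including step counts, it asks for data that cannot yet exist. If it is read as covering only the two questionnaires, step counts have no assessment before week 4. Neither reading gives a pre-randomization baseline.

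**2. What the first available data would be**

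Table 4 gives the weekly dose (MET-min/wk):

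| | Week 1 | Week 4 |
|---|---|---|
| Arm 1 | 300 | 750 |
| Arm 2 | 300 | 1000 |

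Standard care has no supervised exercise during the 16 weeks. The exercise may be walking or jogging, which adds steps directly. Suppose exercise raises the first-week count by δ, and let β be the within-arm slope of follow-up count on first-week count. Using that week as the covariate gives

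adjusted effect = true effect − β × δ,

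so part of the effect is removed from each exercise-versus-standard-care contrast. The prescribed week 1 dose is the same in both exercise arms, so δ is nominally equal there and the 750-versus-1000 contrast is not shifted by this route. By week 4, the first scheduled reading after set-up, the two doses differ.

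**3. Size of the precision loss**

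Let ρ be the correlation of baseline and follow-up steps. The article gives no value, so this is an assumption. Relative to a comparison of follow-up counts alone (variance 1), ANCOVA with a valid baseline has residual variance 1 − ρ². The reduction forgone is ρ².

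| ρ (assumed) | Reduction forgone, ρ² | Residual variance with baseline | Standard error without baseline, 1/√(1 − ρ²) |
|---|---|---|---|
| 0.3 | 9% | 0.91 | 1.05 times |
| 0.5 | 25% | 0.75 | 1.15 times |
| 0.6 | 36% | 0.64 | 1/0.8 = 1.25 times |
| 0.7 | 49% | 0.51 | 1.40 times |
| 0.8 | 64% | 0.36 | 1/0.6 = 1.67 times |

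For ρ of 0.6 to 0.8, 15 patients per arm without a baseline give the precision of 15 × 0.64 = 9.6 down to 15 × 0.36 = 5.4 per arm with one (ignoring the degree of freedom spent on the covariate).

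**The case against.** The strongest reply is that this is a table slip in a condensed article. One row bundles a device with two questionnaires, the screening mark may be meant for the questionnaires alone, and rules on wear days and baseline windows usually sit in the full protocol or analysis plan. It is true that the absence of a detailed wear rule is no fault here. But the printed rows contradict each other, and on either reading the schedule yields no pre-randomization count. Detail held elsewhere could not repair that unless the set-up visit itself were different.

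Other parts of the reply stand, and they limit the point. A reader might infer any of the following, and the document does not support them:

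- **That monitoring of prohibited extra exercise fails.** Adherence to exercise intervention relies on tracker downloads, then an interview and re-education. None of this needs a baseline step count.
- **That steps are the only objective measure of activity.** The tracker also records distance, flights climbed, time in heart-rate zones and energy expended, around the clock. Fitness is tested at screening and week 16.
- **That the arms cannot be compared on steps.** Randomization supports an unbiased comparison of follow-up counts without a baseline term. It is simply not the end point or model that is written.
- **That the plan uses week 1 as the baseline.** Nothing says so. The bias shown above is a risk of filling the gap that way, and it concerns exercise versus standard care.

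**Conclusion.** The point holds as an internal contradiction with a limited reach. As scheduled, all 45 planned patients would lack a step count from before randomization, so this end point cannot be formed as a change from a pre-randomization value, nor its ANCOVA fitted with such a covariate. This rests on reading the schedule as printed, not on knowledge of what is done at the site.

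Only the tracker component is affected. IPAQ and DASI can be collected at screening, diet has its own screening measurement, and the MRI-PDFF result and the key secondary end points are untouched. The sample size does not rest on step counts.

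The cost is the precision forgone, 36% to 64% of residual variance under the assumed correlation of 0.6 to 0.8 and less if the correlation is lower, together with the loss of an objective pre-trial reference for standard-care activity. It is worth correcting because the remedy is cheap and the obvious improvised substitute would be affected by treatment.

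**What to change.** **Patients not yet randomized.** In Table 2, move tracker set-up from visit 2 to the screening visit. Define the baseline as mean daily steps over a stated wear period before randomization, for example at least 7 worn days. Screening lasts up to 28 days, so there is room. The fitness test that sets the tracker's heart-rate zones is already marked at screening, so the zones do not tie set-up to week 0.

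**Patients already randomized.** Recruitment is described as under way, and a schedule change cannot supply these patients with a baseline. For them, restate the end point as a between-arm comparison of follow-up step counts, adjusted for diabetes status and without a baseline step term. State that days after randomization will not be used as the baseline. If both kinds of patient end up in the trial, say before the data are examined which analysis is the main one for this end point.

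**Cost.** Screening gains a minimum wear time, which the article does not now impose. Trackers go out one to four weeks earlier, and some must be recovered from patients who fail screening. The restated end point costs only a change of wording and gives up the precision shown above.
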